### Outcomes

The primary outcome is correct patient assessment and treatment-plan-defining care in the first 24 h. This endpoint was evaluated as the proportion of all patients admitted with pneumonia who were eligible for treatment with orally administered amoxicillin based on guideline recommendations (increased age-specific respiratory rate or lower chest wall indrawing in a child with history of cough or difficulty breathing) who are correctly classified and treated using orally administered amoxicillin at 24 h. The secondary outcome will be measured over the course of the admission as any change in treatment for pneumonia after the first 24 h. This change from orally administered amoxicillin to intravenously administered antibiotics for pneumonia during inpatient stay is considered a proxy for treatment failure rate..

### Data collection, management, and analysis

#### Data collection methods

The trial data were collected at the point of hospital discharge by data clerks using existing data collection tools developed for data collection within the CIN [7, 8]. The clinical tool has been in development and use for some time, and contains information on biodata, clinical features on admission and history of illness [18]. Further data collection procedures were designed for data collection on laboratory investigations, initial antibiotic treatment and supportive care including oxygen therapy for pneumonia, and discharge outcomes after adaptation from previous studies [19]. Prior to the trial commencement the general CIN tools were adapted to capture outcomes to be used for assessing the new pneumonia treatment policy that were not previously contained in the treatment guidelines, e.g., (1) revised pneumonia severity classification and (2) formulation and dosage of dispersible amoxicillin tablets. At the end of each working day (Monday to Friday) a clerk will enter data from inpatient paper records of pediatric discharges into an electronic tool designed using REDCap, a non-proprietary software for clinical data capture. Data for children discharged on weekends will be entered at the start of the new week. All data clerks working in the CIN were retrained on capturing pneumonia data following changes in the pneumonia treatment guidelines. In addition, revised data collection manual and standard operating procedures were available in all sites.

#### Data management

At the end of each day the data clerk at each site synchronized data to a centralized server hosted at the KEMRI-Wellcome Research Program. Data quality was ensured through running error-checking scripts on a daily basis both in the sites and at the centralized trial server and conducting three rounds of external data quality assurance (DQA) during the 9-month trial period. The cleaning scripts raised error queries related to possible out-of-range values and implausible and inconsistent entries. Using the daily error logs generated by the scripts, a data manager flagged the potential errors with the clerk who verified the entries and cleaned any errors. Once all errors had been resolved all data were then archived in the centralized server with the primary data generated at each hospital retained within the hospital. During the periodic external DQA, a team from the KEMRI-Wellcome Trust Research Program visited each site and conducted an independent re-entry of approximately 10% randomly sampled patient data that had been entered by the clerk in the preceding 3 months. The independent entries were then compared to the corresponding existing entries in the database with the aim of determining data quality and identifying database fields where agreement was low for discussion with the data entry clerks.

All hospitals will continue to participate in network activities which will encourage retention of hospitals in the trial. Individual participant retention and follow-up were not major concerns in this trial because the data were collected on discharge through abstracting admission events contained in medical records.

#### Statistical methods

Characteristics of patients and hospitals in the analysis will be compared according to treatment arm to evaluate the ability of randomization to deliver balance across hospital groups. Any variables that show imbalance between intervention groups will be considered for adjustment in comparison of intervention effect.

The primary comparison of correct classification and treatment of pneumonia will include all patients meeting clinical criteria for pneumonia (but not severe pneumonia) recruited in the trial during the 9-month period. The primary outcome will be a binary variable indicating whether a child admitted with non-severe pneumonia is correctly classified and treated based on new guideline recommendations. To account for the cumulative effect of feedback delivered at different time points during the 9-month intervention, the primary comparison will be adjusted for time between commencement of intervention and patient recruitment. A hierarchical logistic regression analysis will be conducted with the primary outcome (correct pneumonia classification and treatment) and independent variables including treatment arm, time (as a continuous variable), and both patient level and hospital level and adjusting for any imbalances in patient characteristics. The model will account for clustering by including a random effect for hospital. The change in performance over time will be included as a time trend. Tests for significant differences in the time trend between the treatment arms will be examined by including an interaction term between the treatment group and the time variable.

In separate sensitivity analysis, multiple imputation will be used to handle missing data and allow classification of all pneumonia patients. Bayesian bootstrap predictive mean matching will be conducted 50 times to impute missing data for signs required to classify pneumonia severity. After imputation, diagnostic checks will be conducted to compare the distribution of imputed and observed data. The modeling approaches used in the primary trial analysis will be repeated after imputation on each imputed dataset and the estimates combined using Rubin’s rules.

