### Study design

We designed a parallel-group, pragmatic, cluster randomized trial to be conducted in 12 hospitals over a 9-month period with interim analysis at 6 months in case of a more marked intervention effect than we are expecting. At the time of the trial design all the 12 hospitals were participating in a clinical network in which standardized audit and feedback had been delivered to all sites for more than 12 months; therefore, providing context for testing an enhanced feedback intervention. The intervention was designed to examine whether specific characteristics of feedback (frequency, goal setting, and action planning) can result in greater impact (Fig. 2). The intervention targets improvements in hospital uptake of new pneumonia treatment policy; therefore, hospitals (and entire pediatric care teams) rather than individual clinicians will be randomized to intervention [15].

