### Randomization

The trial will be conducted in 12 geographically dispersed hospitals participating in the CIN. Restricted randomization was used to allocate the participating hospitals into the intervention and control arms to ensure that balance is achieved between the two treatment arms with respect to number of patients admitted as inpatients with pneumonia, and geographical location (also a proxy for malaria prevalence or disease case-mix) [15]. The hospitals were grouped into four categories using information on geographic location (central or western region) and monthly average number of patients admitted with pneumonia (<30 or ≥ 30 per month) collected within the clinical network during the year preceding the intervention. Five hospitals were located in the western region, while seven hospitals had at least 30 patients admitted with pneumonia per month. A statistician used *R* statistical software to generate the 924 possible allocations for assigning 12 clusters to two treatments with six clusters allocated to each treatment arm. We defined a balancing criteria based on the two selected covariates and determined that approximate balance would be achieved by including allocations which had in each treatment arm either two or three hospitals located in the western region and three or four hospitals admitting < 30 pneumonia cases per month. The *R* computer program was used to assess each allocation against the balancing criteria for geographic location (2:3 or 3:2 split between the arms) and monthly number of patients admitted with pneumonia (3:4 or 4:3). There were a total of 536 allocations that met the criteria and represented relative balance between the intervention and control arms with respect to desired allocation ratio. Computer-generated random numbers were used to select one of these allocations at random. Hospitals in the randomly selected allocation were assigned to treatment and those not included in the allocation were assigned to the control group. Allocation was based on clusters rather than individual patients and allocation concealment was conducted at the cluster level. The trial statistician concealed the sequence from investigators until training on the new policy was conducted in all hospitals and the intervention was assigned. Blinding of investigators and health care providers after intervention assignment was not feasible in the trial because the delivery of enhanced feedback on pneumonia care provided was done by investigators and the target of this feedback was the health care providers. However, for the interim analysis the statistician was blinded to treatment arm allocation.

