
### Sample size

Based on the primary outcome of correct pneumonia classification and treatment we performed a power calculation to determine the feasibility of conducting the trial within the period of the network’s funding cycle using a fixed number of hospitals recruited into CIN. Using data collected during the first year of CIN operation we determined that: on average, 616 (range 310–898) children are admitted to each hospital annually with pneumonia and of these 150 children (range 78–228) are eligible for treatment with amoxicillin. We estimated that if we evaluate the primary outcome 9 months after trial commencement with six hospitals per arm then at least 680 patients with pneumonia requiring amoxicillin treatment will be enrolled per arm. Assuming an average cluster size of 113 patients and an intracluster correlation coefficient (ICC) of 0.2 (corresponding to a variance inflation factor (VIF) of 15.8 and based on calculation of pneumonia classification and treatment within CIN hospitals), a Type-I error rate of 5%, and 90% power we will be able to detect a two-fold increase in the odds of correct pneumonia classification and treatment over 9 months if correct pneumonia classification and treatment is 30% in the control group following the treatment policy change. To ensure that the desired sample size is attained within each hospital, all eligible patients will be recruited in the hospitals with a workload less than 3000 annual pediatric admissions. For hospitals with a very high annual workload (at least 4000 admissions) a random sample will be selected using computer-generated random numbers applied to eligible participants.

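### Covariates are to be chosen by observed imbalance, and the two factors that restricted the randomisation (region and pneumonia volume) are not named in the primary model

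*Protocol article*

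**What the plan says.** Under Randomization, the protocol article restricts allocation "to ensure that balance is achieved between the two treatment arms with respect to number of patients admitted as inpatients with pneumonia, and geographical location". It groups hospitals "using information on geographic location (central or western region) and monthly average number of patients admitted with pneumonia", with the volume cut at 30 per month, and accepts 536 of the 924 possible allocations. Region is described there as a stand-in for malaria prevalence or case-mix, so the authors treat it as possibly prognostic.

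Under Statistical methods, patient and hospital characteristics are compared by arm, and "Any variables that show imbalance between intervention groups will be considered for adjustment in comparison of intervention effect". The primary model is a hierarchical logistic regression with "independent variables including treatment arm, time (as a continuous variable), and both patient level and hospital level and adjusting for any imbalances in patient characteristics". On clustering: "The model will account for clustering by including a random effect for hospital". Region and pneumonia volume do not appear by name in the analysis.

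**The concern.** When randomisation is restricted on a factor, the design removes most of that factor's contribution from the difference between arms. If the analysis omits the factor, its variance stays in the residual between-hospital term. The standard error is then too large for the contrast actually estimated, and a test using it is conservative.

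An imbalance-triggered rule points the wrong way here, because factors held near balance by design are the least likely to be flagged. The rule also has no variable list and no threshold, and it commits only to considering adjustment. Among 12 hospitals, chance differences will be common. Investigators know the allocation, and the article states blinding of the statistician for the interim analysis only. The primary estimate could therefore depend on which differences someone decides to act on. Under Discussion, the article itself concedes that few clusters may limit its ability to detect effects, so avoidable losses matter.

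**Working it through.** **1. The allocation count.** Inputs (Randomization): "Five hospitals were located in the western region, while seven hospitals had at least 30 patients admitted with pneumonia per month"; 12 hospitals, six per arm. I required 2 or 3 western hospitals and 3 or 4 high-volume hospitals per arm. A 3:4 split fits only the seven high-volume hospitals, since five are below 30. Enumerating all 924 allocations by the number of western hospitals that are high-volume:

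| Western and high-volume | 0 | 1 | 2 | 3 | 4 | 5 |
|---|---|---|---|---|---|---|
| Acceptable allocations | 700 | 580 | 530 | 518 | 536 | 600 |

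The stated 536 reproduces only with four, so that layout is used below.

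**2. The effect the protocol assumes.** Inputs (Sample size): control 30%, odds ratio 2, ICC 0.2, 113 patients per hospital, six hospitals per arm.
- Control odds 0.30/0.70 = 0.4286; doubled, 0.857; intervention rate 0.857/1.857 = 46.2%. Difference 0.1615.
- Between-hospital SD at the mean rate 0.381: √(0.381 × 0.619 × 0.2) = 0.217. Ratio 0.1615/0.217 = 0.74.
- Logit scale: ln 2 / √(0.25 × π²/3) = 0.693/0.907 = 0.76.

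So the effect is about 0.75 between-hospital SD.

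**3. Starting power.** Variance of the difference in hospital means: (0.21 + 0.2485) × (0.2 + 0.8/113) / 6 = 0.0158, SE 0.126. Noncentrality 0.1615/0.126 = 1.28. On 10 degrees of freedom, two-sided 5% (sidedness is not stated), power is 21%.

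The stated 90% does not reproduce. With 113 patients and ICC 0.2 the variance inflation is 1 + 112 × 0.2 = 23.4, not 15.8. A two-proportion calculation gives 24% at 23.4 and 34% at 15.8. That is a separate matter, but it explains why the powers here are low.

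**4. Effect of omitting the factors.** Simulated hospital-level t-tests over the 536 allocations, with the inputs above. The share of between-hospital variance explained by region and volume is my assumption.

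| Share explained | Type I error, unadjusted | Type I error, adjusted | Power, unadjusted | Power, adjusted |
|---|---|---|---|---|
| 0% | about 5% | about 5% | 21% | 19% |
| 30% | about 2.6% | about 5% | about 17% | 25% |
| 50% | about 1.2% | about 5% | about 16% | 33% |

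The unadjusted figure at 50% varies with how the two factors share the variance. It is about 16% if they act in opposite directions and about 14% if they act together. The adjusted figures barely move.

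**5. Uncorrected inference.** With intercept, arm, region and volume, 12 hospitals leave 12 − 4 = 8 degrees of freedom. A maximum-likelihood variance divides by 12, so a Wald test at 1.96 rejects when |t| exceeds 1.96 × √(8/12) = 1.60. On 8 degrees of freedom that happens about 15% of the time under the null. With a third hospital covariate the cut-off is 1.96 × √(7/12) = 1.50 on 7 degrees of freedom, about 18%. An unbiased variance referred to the normal still gives 8 to 9% with two covariates.

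**The case against.** The strongest reply is that the model sentence mentions patient level and hospital level. A noun seems to be missing, and the natural reading is that hospital covariates are planned. Region and volume are the only hospital covariates the article defines, and naming covariates is often left to a fuller analysis plan. This stands in part: a reader should not infer that hospital-level adjustment has been ruled out. It does not dispose of the point, because the article states a selection rule, and that rule suits a restricted design badly.

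Second, a reader might infer that the rule is bound to leave these two factors out. It is not. The permitted splits are 2:3 and 3:4, that is 33% v 50% western and 50% v 67% high-volume, and hospital characteristics are among those compared. Either factor could be flagged. The rule tends to omit them; it does not guarantee it.

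Third, much larger gains can be produced. At an effect of 1.2 between-hospital SD, power rises from about 43% to 55% at 30% explained and from about 40% to 70% at 50%. The Sample size section does not support that effect; its inputs imply about 0.75 SD.

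Fourth, a reader might infer that each hospital's baseline on the primary outcome is already held. The article says "standardized audit and feedback had been delivered to all sites for more than 12 months", and that the ICC was "based on calculation of pneumonia classification and treatment within CIN hospitals". But before 2016 a three-grade classification applied and many of these children received injectable penicillin (Background), and the collection tools were adapted to the revised classification only before the trial began (Data collection methods). The new indicator could not be fully observed beforehand, so any pre-trial measure is a proxy.

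Fifth, the calculations use hospital-level linear tests, not the planned random-effect logistic model. This is fair: they show direction and rough size only.

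**Conclusion.** The point holds as a correctable weakness in the stated analysis. The adjustment rule is ill-matched to the restricted randomisation and leaves the covariate set open.

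For a hospital-level t-test at the protocol's own effect, omitting region and volume gives power of about 16 to 17% against 25 to 33% when they explain 30 to 50% of between-hospital variance. Type I error is then about 2.6 to 1.2% rather than 5%. If they explain nothing, adjusting loses about 2 points. These figures rest on ICC 0.2, 113 patients per hospital, a two-sided 5% test, four high-volume western hospitals, and assumed shares explained.

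A reader might infer that omitting the factors produces false positives. It does not: with correct small-sample inference the error is conservative. Inflation would come from uncorrected Wald tests, and the article does not say which inference will be used.

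**What to change.** Replace the imbalance rule with a fixed set, settled before outcomes are examined by arm:

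- Enter region (western or central) and monthly pneumonia volume (<30 or ≥30) in the primary model, whatever the observed balance. Name any patient-level covariates in advance.
- In the same text, state that the test of the arm effect uses a small-sample degrees-of-freedom correction or a permutation test over the 536 acceptable allocations. The covariates should not be adopted without this.
- Report characteristics by arm descriptively. Put any imbalance-driven adjustment in a sensitivity analysis.
- Optionally add one prespecified hospital-level measure of pre-policy pneumonia performance from existing network data, if available, described as a proxy.

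The cost is analysis wording; region and volume are already held. Two hospital-level degrees of freedom are spent (10 to 8), or three with the optional measure (10 to 7), and about 2 points of power are lost if region and volume prove unrelated to outcome.

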Among the limitations of the trial is the relatively limited number of clusters. This may limit our ability to detect effects and may raise concerns as to the external validity of any findings. It is important to note that most cluster trials in health conducted in low- and middle-income countries to date have involved randomization of communities and hospitals have rarely been used as randomization units. Additionally, there are issues related to the delivery of effective feedback that deserve attention but which this study could not address. These questions include, but are not limited to, the ideal duration of feedback interventions, and alternative suggested key components of feedback that could enhance performance but that were not examined in this trial [4]. In our case, the duration of our intervention was informed by sample size considerations (power, significance level, effect size), and the participating facilities’ pediatric workloads. Inefficiencies may occur if the duration determined under these assumptions is considerably longer than the ideal duration of feedback. Conversely, a short intervention duration might omit the effect of feedback that is lesser in magnitude but still useful at a system level. Providing evidence to address these issues will require continued methodological developments, possibly involving adaptive designs to suit the dynamic nature of feedback interventions.

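### With 12 hospitals, the primary random-effect logistic model needs a named small-sample test; uncorrected, its nominal 5% size is generally about 7.5% to 10%

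*Protocol article*

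**What the plan says.** The Statistical methods section of the protocol article specifies a hierarchical logistic regression for correct classification and treatment. Its independent variables are treatment arm, continuous time, and patient- and hospital-level variables, with adjustment for imbalances. On clustering it says "The model will account for clustering by including a random effect for hospital". It names no type of test (Wald, likelihood ratio or other), no degrees of freedom and no permutation or hospital-level test.

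The Randomization section describes an allocation "with six clusters allocated to each treatment arm", restricted on region and pneumonia volume: "There were a total of 536 allocations that met the criteria". The Sample size section sets "a Type-I error rate of 5%, and 90% power". The Discussion acknowledges "Among the limitations of the trial is the relatively limited number of clusters", and gives as consequences a reduced ability to detect effects and doubts about external validity.

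**The concern.** The arm effect is estimated by comparing six hospitals with six others. At the planned intracluster correlation, almost all its variance lies between hospitals, so what counts is how well 12 hospitals estimate the between-hospital variance. Ordinary large-sample inference from a random-intercept model goes wrong in two ways here. Maximum likelihood underestimates that variance, and a normal or chi-square reference ignores the uncertainty in the estimate. Both make p-values too small and confidence intervals too narrow.

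The Discussion recognises only the loss of power from few clusters. The false-positive risk runs the other way: a p-value just under 0.05 in favour of enhanced feedback would be weaker evidence than it appears.

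**Working it through.** **Inputs.** From the Sample size and Randomization sections: 12 hospitals, 6 per arm; average cluster size 113; ICC 0.2; control proportion 30%; nominal size 5%. Eligible children number 78–228 per hospital per year, or about 58–171 over 9 months (× 0.75). Assumptions: a two-sided test, because sidedness is not stated, and several readings of the ICC, because its scale is not stated.

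**The plan's own figures.** The article gives no size other than the nominal 5%. Its variance inflation factor does not follow from its inputs: 1 + (113 − 1) × 0.2 = 23.4, whereas 15.8 corresponds to an ICC of 14.8/112 = 0.132. That is a separate matter, but it is why both ICC values are tried below.

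**How much variance is between hospitals.** On the latent logistic scale, ICC 0.2 gives σ² = (0.2/0.8) × π²/3 = 0.822. The sampling variance of one hospital's log-odds is about 1/(113 × 0.3 × 0.7) = 0.042. So about 95% of the variance of a hospital's result is between hospitals, and treating the data as 12 hospital summaries is a good approximation.

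**Closed form, 12 summaries, 10 df.** Let t be the ordinary two-sample statistic. A valid 5% test rejects when |t| > 2.228.

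- ML Wald z: the variance uses divisor 12 instead of 10, so z = t√(12/10). |z| > 1.96 means |t| > 1.96 × √(10/12) = 1.789, and P = 10.4%.
- Likelihood ratio: 12 ln(1 + t²/10) > 3.84 means |t| > √(10 × (e^(3.84/12) − 1)) = 1.942, and P = 8.1%.
- z on an unbiased variance: P(|t| > 1.96) = 7.8%.

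With hospital-level covariates, 10 becomes 9 or 8 in these formulas:

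| Hospital-level covariates | ML Wald z | Likelihood ratio |
|---|---|---|
| 0 | 10.4% | 8.1% |
| 1 | 12.4% | 9.8% |
| 2 | 14.8% | 12.1% |

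**Simulation of the model itself.** A hospital random-intercept logistic model was fitted by maximum likelihood (15-point adaptive quadrature) under no effect, with 4,000 trials per setting (Monte Carlo SE about 0.5 points):

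| Setting | Wald z | Likelihood ratio | Wald, t on 10 df | t test on hospital log-odds |
|---|---|---|---|---|
| Latent ICC 0.2, equal sizes | 10.0% | 7.5% | 6.6% | 5.2% |
| Latent ICC 0.2, sizes 58–171 | 9.6% | 7.5% | 6.2% | 4.4% |
| Proportion-scale ICC about 0.22, equal sizes | 10.3% | 8.1% | 6.8% | 4.8% |
| Proportion-scale ICC about 0.22, sizes 58–171 | 9.8% | 7.3% | 6.1% | 4.5% |
| Latent ICC 0.132, equal sizes | 10.6% | 8.1% | 6.7% | 5.1% |

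These runs used simple allocation and left out time and patient covariates.

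**Restricted randomization.** With 5 western hospitals and 7 admitting at least 30 cases a month, exactly 536 allocations result when 4 of the 5 western hospitals are in the higher-volume group. Drawing from that set (hospital-level normal approximation, 20,000 null draws per setting):

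| Balancing factors | ML Wald z | Likelihood ratio | t, residual df |
|---|---|---|---|
| Not prognostic, unadjusted | 10.6% | 8.4% | 5.3% |
| Each shifts hospitals by 0.5 SD, unadjusted | 8.3% | 6.4% | 3.9% |
| Each shifts hospitals by 1 SD, unadjusted | 4.7% | 3.3% | 1.7% |
| Both adjusted, at any of these strengths | 14–15% | about 12% | about 5% |

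**The case against.** The strongest objection is that the article never says the test is Wald z. A reader might infer that the plan has a false-positive rate of 9–10%, about twice the nominal rate. That figure belongs to one assumed implementation; a likelihood-ratio test gives 7.5–8%, and a Wald test with t on 10 df gives 6–7%. All three fit the text.

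A reader might also infer that small-sample inference has been ruled out. The document does not support that. It is a condensed article, a degrees-of-freedom method is often left to an analysis plan, and none is shown here. The Discussion's silence on type I error does not show that a correction was rejected. A hospital random effect is itself an accepted way to handle clustering.

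Two further points stand. No hospital-level covariate is named or counted, so the figures with one or two are conditional. Restricted randomization on prognostic factors left unadjusted lowers the size and can remove the excess.

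What remains is that the primary method, followed as written with ordinary software output, generally gives a test above 5%. Restriction rescues it only if both factors are strongly prognostic and omitted, whereas adjusting for them makes the excess larger. The section specifies its imputation in detail (method, 50 imputations, pooling rule), so naming the primary test would not be out of place.

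**Conclusion.** The point holds as a conditional statement. Unless a small-sample correction is applied, and the article states none, the nominal 5% primary test has a true size of about 7.5–8% (likelihood ratio) to about 10% (ML Wald z). This hardly changes over the ICC values and cluster sizes tried. It rises to about 10–12% with one hospital-level covariate and 12–15% with two. It could fall to about 5% or below if region and volume are strongly prognostic and unadjusted.

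The direction is well supported for most versions of the stated analysis; the exact figure is not fixed, because the test, the covariates and the strength of the balancing factors are unknown. The simulations omit time and patient covariates, and the covariate and restricted-allocation results rest on a hospital-level normal approximation. Nothing here shows that the eventual analysis will be uncorrected.

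**What to change.** Keep the hierarchical logistic model for the odds ratio and name the primary test in advance. Either of these would do:

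- A permutation test of the arm effect from the stated model over the 536 admissible allocations, with the confidence interval by test inversion. It respects the restriction and has correct size whether or not the balancing factors are prognostic. The smallest possible two-sided p-value is about 2/536 = 0.004.
- A hospital-level analysis (log-odds or covariate-adjusted residuals) with t on 10 df less the number of hospital-level covariates.

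A t reference on residual df within the stated model is only a partial remedy: about 6–7% without covariates, and 10.2% in a smaller simulation (600 trials) with two hospital-level covariates. Whichever test is chosen, fix the hospital-level covariates in advance, since each one uses a degree of freedom. If an analysis plan already names a valid method, a cross-reference is enough.

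For the permutation test, use the stored list of allocations. The Randomization section's prose applies the three-or-four split to hospitals below 30 cases, but only 12 − 7 = 5 hospitals are in that group, so the split can apply only to the seven larger ones.

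The cost is a sentence or two and a short R program, as the allocations were already enumerated. Confidence intervals become somewhat wider. The hospital-level t test can also be conservative if strongly prognostic balancing factors are left out (1.7% in the most extreme case above).
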